## Abstract

**Background:**

Targeted radiopharmaceutical therapy (TRT) offers a promising approach for cancer treatment by delivering radiation directly to tumor cells while sparing healthy tissues. Accurate dosimetry of organs and tumors is crucial to optimize therapeutic efficacy and minimize toxicity, particularly for dose-limiting organs such as the kidneys. Although routine dosimetry using single-photon emission computed tomography (SPECT) is recommended per guidelines, its widespread clinical application remains limited owing to a lack of consensus on the optimal frequency and timing of SPECT scans for accurate dosimetry, which leads to variability in clinical practice and hinders robust dose–response relationships. Furthermore, absorbed dose calculations rely on software-specific curve-fitting models. Thus, discrepancies in dose estimates among different simulation software programs pose a significant challenge to standardizing dosimetry workflows.

**Objective:**

We aimed to explore the optimal SPECT imaging schedule, evaluate differences among simulation software programs, and establish a standardized protocol for future epidemiological research to define organ tolerance doses and facilitate wider adoption of personalized TRT regimens.

**Methods:**

This exploratory observational trial will determine the optimal SPECT imaging protocol and consistency of dosimetry estimates using software programs for Lu-177-DOTATATE therapy in patients with neuroendocrine tumors. In a single treatment cycle, SPECT imaging will be performed at 4, 24, 96, and 168 hours following Lu-177-DOTATATE administration. The true absorbed dose cannot be directly measured; therefore, doses calculated using all time points (the 4-point method) for each patient will be used as the reference standard and compared with estimates derived from 1- to 3-point methods. Consequently, 15 dose simulations will be conducted per patient. This study implements a 5+5 design (rule-based design). The primary endpoint is the incidence of dose errors for each patient across different dose-calculation software systems. The kidney absorbed dose will be the primary focus of evaluation, with secondary analyses including tumor and other organ dosimetry. In principle, a dose error of <5% will be considered acceptable in each software system, depending on the absolute dose level. Differences among software systems and between patients will be evaluated using descriptive statistical methods. The study was approved by the Tokushukai Group Ethics Committee (Approval No. 2447).

**Results:**

Recruitment began on March 5, 2024, and 4 participants have been enrolled as of September 2025. Data collection is expected to be completed by February 2027, with the study results anticipated in August 2027.

**Conclusions:**

This study will evaluate whether simplified SPECT imaging protocols can maintain dosimetric accuracy while reducing the burden on patients and providers. It will also compare absorbed dose estimates across software programs to assess consistency and reliability as a reference. Findings will be disseminated through open-access peer-reviewed journals and relevant conferences and events.

## Introduction

Targeted radiopharmaceutical therapy (TRT) offers a promising cancer treatment approach by delivering radiation directly to tumor cells while minimizing exposure to surrounding healthy tissue. These radiopharmaceuticals, composed of radioactive isotopes linked to tumor-targeting molecules, are particularly effective for advanced cancers and are being explored for a wider range of malignancies [1-4]. Notable examples include Lutetium-177 (Lu-177)-DOTATATE for neuroendocrine tumors (NETs) and Lu-177-prostate-specific membrane antigen for metastatic castration-resistant prostate cancer [3,4]. Despite TRT’s expanding applicability, standardized methods for assessing absorbed doses and defining normal tissue tolerance thresholds remain underdeveloped.

Current guidelines from the European Council Directive 2013/59 (Article 56) and the European Association of Nuclear Medicine/Medical Internal Radiation Dose recommend routine assessment of absorbed radiation doses in each organ and tumor for patients undergoing TRT [5]. This dosimetry typically employs sequential quantitative single-photon emission computed tomography (SPECT) [5]. Accurate image quantification is crucial, as any underestimation or overestimation of absorbed doses can significantly affect clinical decisions and patient safety [5-7]. While SPECT images are routinely corrected for factors such as photon attenuation, scatter, and blurring to ensure quantitative accuracy [5-7], the widespread clinical application of standardized SPECT-based dosimetry remains limited.

Two primary challenges hinder the routine and standardized implementation of TRT dosimetry. First, there is no consensus on the optimal number or timing of SPECT scans. Accurate time–activity curves, which are essential for precise dose estimation, benefit from frequent imaging, particularly shortly after injection [8]. However, increasing SPECT scan frequency also raises patient burden, owing to additional radiation exposure, prolonged imaging time, and psychological stress, and strains health care resources. Consequently, current clinical practices for SPECT timing vary significantly, with protocols ranging from multiple scans (eg, 24, 96, and 168 hours post-injection) to a single scan at a specific time point [5,9-12]. This variability is particularly problematic for dose-limiting organs such as the kidneys, where precise dosimetry is critical to minimize toxicity. Second, absorbed dose calculations in TRT rely on various simulation algorithms, yet their dose estimates often lack universal validation. As a result, a dose reported by one software program may not be directly comparable with that from another, complicating the standardization of dosimetry workflows and hindering the establishment of robust dose–response relationships.

This study aims to identify the optimal SPECT imaging schedule for accurate TRT dosimetry and evaluate the differences in dose estimates among various simulation software programs. Ultimately, we seek to establish a standardized protocol for TRT dosimetry to support future epidemiological research, aid in defining organ tolerance doses, and facilitate the wider adoption of personalized TRT regimens, thereby optimizing therapeutic efficacy and minimizing toxicity.

## Methods

### Aims and Objectives

This study, conducted at Shonan Kamakura General Hospital, aims to optimize the SPECT imaging schedule, evaluate differences among simulation software programs, and develop a protocol suitable for epidemiological studies to define dose constraints for normal organs in Lu-177-DOTATATE therapy. Specifically, we will investigate whether the standard 4-time-point protocol could be reduced to 1-, 2-, or 3-scan protocols without compromising dosimetric accuracy. The purpose of this study is to explore practical time points for dosimetry within a single treatment cycle. Inter-cycle variability will be examined in subsequent studies after optimal time points are established in this study.

The primary endpoint is to evaluate the effect of scan reduction on the estimated absorbed dose to the kidneys, given that renal toxicity—particularly radiation-induced nephropathy—is the primary dose-limiting factor. Secondary endpoints include comparing tumor and normal organ dosimetry across imaging protocols and analyzing dose variations among software programs to assess consistency and reliability.

### Design

This open-label, single-institution exploratory observational study will recruit patients with neuroendocrine tumors undergoing Lu-177-DOTATATE therapy. Gamma emissions from normal organs and tumors will be measured using SPECT imaging at 4, 24, 96, and 168 hours following radiopharmaceutical administration. These images will serve as inputs for simulation software to calculate absorbed doses to normal organs and target tissues.

 This study adopts the 4-time-point SPECT protocol (4-point method) as the reference standard for each patient within each software program. Doses calculated after omitting 1‐3 time points (1-, 2-, and 3-point methods) will be compared with the 4-point dose within each program. The evaluation frameworks for each method are summarized below. Fifteen dose simulations will be conducted per patient. Data collection will span from March 2024 to February 2027.

For the 4-point method, dosimetry calculation will be performed using SPECT images taken at 4, 24, 96, and 168 hours. For the 3-point method, dosimetry calculation will be performed using SPECT images taken at 24, 96, and 168 hours; 4, 9, and 168 hours; 4, 24, and 168 hours; and 4, 24, and 96 hours. For the 2-point method, dosimetry calculation will be performed using SPECT images taken at 4 and 24 hours; 4 and 96 hours; 4 and 168 hours; 24 and 96 hours; 24 and 168 hours; and 96 and 168 hours. For the 1-point method, dosimetry calculation will be performed using SPECT images taken at 4 hours; 24 hours; 96 hours; and 168 hours post-injection

If dose discrepancies remain within acceptable limits, the simplified protocol will be considered for future trials. Additionally, absorbed doses calculated using each program will be compared across algorithms.

### Study Design Considerations

This exploratory observational study will evaluate various SPECT imaging time-point protocols and dosimetry software programs in patients undergoing Lu-177-DOTATATE therapy. Patient randomization is not applicable because the objective is to evaluate dosimetric methods against a reference standard in a real-world clinical setting rather than to compare treatment groups.

This is an open-label study. Blinding of participants or investigators will not be performed, as the primary focus is on technical comparisons of dosimetry methodologies and software programs. Blinding of imaging protocols or software analyses would be impractical and irrelevant for assessing dosimetric accuracy in this context.

### Safety and Data Monitoring

This study is designed as an exploratory observational trial and primarily involves the acquisition of additional SPECT/computed tomography (CT) images as part of the standard clinical protocol for Lu-177-DOTATATE therapy. As such, the research interventions are integral to routine clinical care and introduce minimal to no additional risks to participants beyond that associated with standard Lu-177-DOTATATE therapy.

The potential for additional radiation exposure from the extra SPECT/CT scans is considered negligible and will be kept as low as reasonably achievable, in accordance with the recommendations of the International Commission on Radiological Protection [13]. Any adverse events related to Lu-177-DOTATATE therapy will be managed and reported by the treating physicians according to standard clinical practice and existing institutional guidelines [14], and not as part of this study protocol, as the focus of this study is solely on dosimetry methodology.

Given the non-interventional and low-risk nature of this observational study, an independent data monitoring committee will not be established.

### Data Handling and Exclusions

All acquired SPECT/CT images that meet technical quality control standards will be included in the dosimetry analysis. Data points, including individual SPECT scans, may be excluded if deemed technically inadequate—owing to motion artifacts, hardware malfunction, or incomplete acquisition—after review by a medical physicist, as these issues could compromise dose calculation accuracy. All exclusions will be thoroughly documented and reported.

### Data Management

The data will be entered and stored using Microsoft Excel software, cross-checked in pairs, saved on an encrypted computer, and backed up.

### Statistical Analyses and Sample Size

This study implements a 5+5 design, also known as a rule-based design [15]. The primary endpoint is the dose error incidence for each calculation algorithm. Figure 1 presents the decision-making workflow. The assumed dose error incidence in this study is set to be ≤5%; based on this assumption, the required number of eligible patients will be modified using the 5+5 design [16]. If the incidence (dose error per patient ≤ threshold) is ≤5% within the workflow, false-negative results will be observed in ≤23% of trials. If the incidence is ≥30%, false-positive results will occur in ≤17%.

Dose error below the predefined threshold will be considered acceptable for each calculation algorithm. The primary threshold will be set at 5%, following the International Commission on Radiation Units and Measurements Report 83 guidelines [17], which recommend that overall dosimetric uncertainty should ideally be within ±5%. For regions with absorbed doses <5 Gy, where larger errors are generally observed, the threshold will be relaxed to 10% [18]. A simplified method will be deemed “acceptable” if, in all five cases, the absorbed dose estimated by each software program falls within the threshold (5% or 10%, depending on the regional dose) when compared with the reference 4-point method. If multiple algorithms meet the criteria, priority will be given to the algorithm requiring the fewest time points for the subsequent trial. For example, if both the 3-point and 1-point methods meet the criteria, the 1-point method will be selected as the primary candidate. Among algorithms requiring the same number of time points, those incorporating the 4-hour or 24-hour sampling points will be preferred.

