### Dosimetry Methods

#### Dosimetry Protocol

In this study, four quantitative SPECT/CT scans will be performed for dosimetry following the administration of Lu-177-DOTATATE during one of the four treatment cycles. These scans, covering from the neck to the femoral head region, will be acquired over 30 minutes using a Symbia Intevo 6 system (Siemens Healthineers, Erlangen, Germany) equipped with medium-energy general-purpose collimators. To optimize image quality and quantitative accuracy, image reconstruction will be conducted using the ordered subset conjugate gradient minimization algorithm (xSPECT) with a matrix size of 256×256. A Gaussian filter will be applied during image reconstruction. The primary energy peak will be centered at 208 keV (187.6‐229.2 keV). Scatter correction will use the triple energy window method, and attenuation correction will be based on CT. CT images will be acquired at 130 kV and 20 mA using the adaptive dose modulation technique (CARE Dose 4D; Siemens Healthineers). To enable absolute quantification, the gamma camera will be calibrated using a Lu-177 point source. Dose calibration will be performed using serial SPECT/CT acquisitions of Lu-177 point sources in air and in a tissue-equivalent medium to simulate attenuation. Dead time will be determined and corrected based on wide-spectrum counting rates during image acquisition. To simulate absorbed doses in tumors and normal organs, the injected activity (GBq), date and time of TRT administration, and patient weight (kg) will be entered into the dosimetry software.

Subsequently, organ and target absorbed doses will be simulated using at least five commercially available software programs and one newly developed tool: (1) OLINDA/EXM (Hermes Medical Solutions); (2) Dosimetry Toolkit (GE HealthCare Medical Systems and Solutions); (3) Voxel Dosimetry (Hermes Medical Solutions); (4) MIM SurePlan MRT (MIM Software Inc.); (5) RT-PHITS (Japan Atomic Energy Agency); and (6) a newly developed dose calculation program introduced after 2022 (name and developer to be specified once the software is finalized and becomes available during the study period).

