Second, the small sample size (estimated 5‐10 patients) may not capture the full range of pharmacokinetic variability or tumor responses among patients. However, given that 4-time-point measurements impose a substantial burden on patients and health care providers, the limited sample size is unavoidable from a practical standpoint. The study design allows for a false-positive probability of 32% if the incidence (dose error per patient≤ threshold) is ≤20% within the workflow. These dose errors are considered to arise from software-specific curve-fitting models and dose-calculation frameworks. The incidence of such errors will be addressed through cross-validation among multiple software systems. Specifically, simplified time-point methods that demonstrate inconsistencies between software systems will be excluded from consideration in subsequent studies. Third, detailed 4-time-point SPECT imaging is performed in only one treatment cycle per patient, which does not account for potential changes in radiopharmaceutical distribution across subsequent cycles. Inter-cycle variability will be examined in subsequent studies after the optimal time points are determined in the present study. Finally, although multiple simulation software programs are evaluated, not all possible variations in image acquisition parameters or software algorithms are explored. These limitations highlight the need for future multi-institutional validation studies with larger cohorts and longitudinal studies to comprehensively standardize TRT dosimetry. Despite these limitations, this study is expected to provide crucial foundational data to guide the development of robust dosimetry protocols essential for advancing personalized TRT and facilitating large-scale epidemiological research.

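### The unit of the acceptability decision is contradictory and the program list is open, and the stated 23% false-negative rate fits only one program over the first five cases

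*Protocol article*

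**What the plan says.** **Unit of the endpoint.** Statistical Analyses and Sample Size states: "The primary endpoint is the dose error incidence for each calculation algorithm". It adds: "Dose error below the predefined threshold will be considered acceptable for each calculation algorithm". The Abstract (Methods) has a different unit: "The primary endpoint is the incidence of dose errors for each patient across different dose-calculation software systems". Aims and Objectives names the organ: "The primary endpoint is to evaluate the effect of scan reduction on the estimated absorbed dose to the kidneys", and lists dose variation among programs as secondary.

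**Acceptance rule.** Statistical Analyses and Sample Size calls a simplified method acceptable if "in all five cases, the absorbed dose estimated by each software program falls within the threshold". The same section uses the word algorithm for the imaging schedule when it ranks candidates: "priority will be given to the algorithm requiring the fewest time points for the subsequent trial". The Discussion adds that "simplified time-point methods that demonstrate inconsistencies between software systems will be excluded from consideration in subsequent studies".

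**Number of programs.** Dosimetry Protocol plans "at least five commercially available software programs and one newly developed tool". Six entries are listed; the sixth is to be named when it becomes available during the study.

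**Stage rule.** In the body text, one exceedance among five patients leads to five more cases, and acceptance then needs at least 9 of 10. The Figure 1 caption instead sends four of five to the 4-point method, and extends to ten cases when three or fewer of the five meet the criterion.

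**Error rates.** At most 23% false negatives at an incidence of 5%, at most 17% false positives at 30%, and (Discussion) 32% false positives at 20%. None is tied to a unit or a number of programs.

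**The concern.** A 5+5 rule counts failures among patients, so it needs a definition of a failed patient. Per program, a patient fails in program A if A's reduced-schedule dose misses the threshold against A's own 4-point dose. Jointly, a patient fails if any program misses.

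The two can give opposite results. Suppose two programs each miss once, in different patients among the first five. Per program, each stands at four of five and the body text extends to ten cases. Jointly, two patients have already failed, 9 of 10 is out of reach, and the schedule is unacceptable. Both the verdict and the number of patients (5 or 10) depend on a unit that the text does not fix.

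Under the joint reading, each added program can only make acceptance harder, and the list has no upper limit. Four participants were enrolled by September 2025, so the five-case look was then one patient away.

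**Working it through.** **Inputs.** Exceedance probability p = 5%, 20% and 30%, and the stage rules (Statistical Analyses and Sample Size; Discussion). Number of programs k ≥ 6 (Dosimetry Protocol). Correlation of exceedances between programs: not given, so assumed and varied.

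**1. The plan's own figures.** One program, first five cases only:
- False negative at 5%: 1 − 0.95^5 = 22.6% (stated 23%).
- False positive at 30%: 0.7^5 = 16.8% (stated 17%).
- False positive at 20%: 0.8^5 = 32.8% (stated 32%).

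The stated figures therefore allow no second chance at ten cases. They agree with the Figure 1 caption for one program: there four of five does not lead to acceptance, and three or fewer of five can never reach 9 of 10.

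**2. Body-text two-stage rule, one program.** With q the probability that a patient fails,

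P(accept) = (1 − q)^5 + 5q(1 − q)^4 × (1 − q)^5.

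- q = 0.05: 0.7738 + 0.1576 = 0.9313, false negative 6.9%.
- q = 0.30: 0.1681 + 0.0605 = 0.2286, false positive 23%.
- q = 0.20: 0.3277 + 0.1342 = 0.4619, false positive 46%.

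The move from 23% to 6.9% comes from including the second stage. It has nothing to do with the number of programs.

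**3. Joint rule, 5% as a per-program rate, six programs.** A patient fails if any program fails. Under independence q = 1 − 0.95^6 = 0.2649. Under dependence, q comes from an exchangeable latent normal model with a 5% exceedance in each program. The formula in step 2 then gives:

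| Latent correlation (assumed) | q per patient | False negative |
|---|---|---|
| 0.95 | 0.0837 | 16% |
| 0.8 | 0.1257 | 30% |
| 0.5 | 0.1859 | 50% |
| 0 (independent) | 0.2649 | 70% |

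Seven independent programs give 77%.

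**4. Joint rule, 5% as the per-patient incidence across programs.** Here q = 0.05 by definition and the false-negative rate is 6.9% again, with no inflation.

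**5. A verdict within each program, all required to pass.** Each program fails with probability 0.0687.
- All fail together: 6.9% for any k.
- Independent: 1 − 0.9313^5 = 30% (five programs); 1 − 0.9313^6 = 35% (six).
- Upper bound under any dependence: 5 × 0.0687 = 34%; 6 × 0.0687 = 41%.

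These assume that a program accepted at five cases keeps that verdict if the cohort is extended for another program.

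**The case against.** The strongest reply is that the per-program reading is natural. The Abstract accepts errors under 5% within each software system, the Design section compares reduced schedules with the 4-point dose within each program, and the phrase about each software program can be taken program by program. The kidney statement in Aims and Objectives names the organ and need not compete with the other statements. This stands in part: the joint rule is one reading and not an established fact. It does not settle the unit, because the Abstract's endpoint is per patient across systems, the Discussion drops schedules on which programs disagree, and the word algorithm serves for both schedule and program.

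Three stronger readings are not supported:

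- A reader might infer that the confusion over the unit alone moves the 23% to anywhere between 7% and 70%. The lower end comes from the second stage. The upper end needs exactly six independent programs and a 5% per-program rate, none of which is stated. All programs use the same scans and agreed contours, so positive correlation is plausible. Nor is 70% a ceiling.
- A reader might take 30% or 35% as the worst case when every program must pass its own 5+5 rule. Those are independence results; the bounds are 34% and 41%.
- A reader might suppose that the sixth tool will be picked after the other results are known. The article says only that it will be named once finalized. The open list permits that sequence but does not plan it.

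**Conclusion.** The point holds as an unresolved decision unit combined with an open program list, and should be corrected before the five-case look. The stated 23% is right for one program with no route to acceptance after a miss, as in the Figure 1 caption. It describes neither the body-text two-stage rule (6.9% for one program) nor a joint rule over six programs with 5% per program (about 16% to 50% for latent correlations from 0.95 to 0.5, and 70% under independence). If 5% is meant per patient across all programs, the joint rule adds no inflation and the body-text figure remains 6.9%. The spread rests on assumed correlations and on the body-text rule, which the caption contradicts. Which figure applies cannot be said until the unit, the program list and the stage rule are fixed.

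**What to change.** 1. State one primary endpoint: kidney dose error, per schedule and per program, with the 5+5 verdict made within each program against its own 4-point dose. Use separate words for schedule and program throughout.
2. Carry a schedule forward only if it is acceptable in every program on a list locked before the five-case look. Treat any tool not named by then as exploratory. This keeps the cross-software safeguard in the Discussion.
3. Reconcile the Figure 1 caption with the body-text stage rule.
4. Restate the error rates for the rule chosen. Under the body text, per program: 6.9% false negative at 5%, and 23% and 46% false positive at 30% and 20%. For the all-programs requirement, give the false-negative rate as a range with its dependence assumption: for five programs, 7% if they fail together, 30% if independent and at most 34%; for six, 7%, 35% and at most 41%.

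The cost is wording and a restated set of error rates, with no added patients or scans. A tool that arrives late loses its influence on the verdict but can still be reported.
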